## 3.2 Identification and description of the Investigational Medical Device

The following CE-marked medical device will be used in the clinical investigation:

ARTIS icono biplane angiography system and syngo application software with syngo DynaCT Sine Spin 3-D head imaging protocol.

| Product/Trade Name: | Software version: | Model: | UDI-DI: |
| --- | --- | --- | --- |
| ARTIS icono biplane | VE21 or higher | 11327600 | 04056869063317 |
| syngo application software | VE21D or higher | 11327667 | 04056869124162 |

| Manufacturer: | Facility: |
| --- | --- |
| Siemens Healthcare GmbH  [name]  [name] | Siemens Healthcare GmbH Advanced Therapies  [name]  [name] |

*See Appendix C- US Protocol Amendments

Single Registration Number (SRN): DE-MF-000006122.

There are no deviations from the original CE-marked instructions for use.

**ARTIS icono:**

Intended use: ARTIS, as a family of dedicated angiography systems generating fluoroscopic and radiographic X-ray images, is intended for diagnostic imaging, interventional and minimally invasive therapy.

Its use is indicated for image guidance in non-vascular, vascular, cardiovascular, neurovascular, minimal-surgical, and surgical procedures.

The ARTIS system includes also software options which allow the reconstruction of two-dimensional images acquired with rotational angiography into a three-dimensional image format, as well as options supporting diagnosis, planning, guidance and treatment follow-up.

Indications: In general, all clinical indications of angiography- and fluoroscopic-based procedures within the intended use are applicable for this device.

Contra-indications: For this product there are currently no known contra-indications. However, contra indications for angiography- and fluoroscopy- based procedures apply.

The final decision for use of the medical device in a certain application is made by the physician based on his/her medical knowledge and the risks of the cases involved.

Patient target group(s): The system can be used on all patients, from newborn to geriatric. Patient

weight is limited to the specification of the patient table.

Intended users:

Operator profile: The usage of the system requires specific technical and medical knowledge and skills regarding, at a minimum, radiation protection, safety procedures and patient safety. Those using or working with the system must have acquired such knowledge and skills during their curriculum.

Equipment training: Application training is delivered according to the handover contract. It is mandatory to follow such application training delivered by Siemens Healthineers before any use of the system. The follow-up training, which is necessary due to change of personnel, is in the responsibility of the operator of the system. Any additional training can be requested from Siemens Healthineers.

Device materials in contact with body tissues and/or fluids: Device is not in touch with the human body. The patient mattress is covered with sterile disposable sheets for infection control before patients are placed on the device. The patient may get in touch with the system while being moved onto the table which represents a minor contact before or after the interventional procedure. The materials of the devices and its accessories with a direct contact with skin (skin contact, < 3 hours) are biocompatible according to ISO 10993. The user controls tableside are also covered with sterile drapes for infection control.

**syngo application software:**

Intended use: The syngo Application Software is a medical software for real-time viewing,

image manipulation, 3D-visualization, communication, and storage of medical images and data on exchange media. It can also be configured within a network to send and receive DICOM data. It is used for diagnostic image viewing and post processing and for viewing and post processing during interventional procedures.

It is not intended to be used with digital mammography images.

syngo Application Software provides image guided solutions in the operating room for image guided surgery (by Image Fusion and by navigation systems), image guided solutions in interventional cardiology and electrophysiology and image guided solutions for interventional oncology, radiology and neuroradiology.

syngo Application Software can also be configured with a variety of syngo or Windows-based software options, which are intended to assist the physician in diagnosis, treatment planning and treatment control. It includes commercially available post-processing techniques and OEM options.

The syngo Application Software is a software only medical device. It defines minimum requirements to the hardware it runs on, which can be a standalone workstation or part of another medical device.

Indications: In general, all clinical indications of angiography- and fluoroscopic-based procedures within the intended use are applicable for this device.

Contra-indications: For this product there are currently no known contra-indications.

Intended purpose: The final decision for use of the medical device in a certain application is made by the physician based on his/her medical knowledge and the risks of the case involved.

Patient target group(s): The system can be used with patients which are newborn to geriatric.

Intended users:

Operator profile: The usage of the software requires specific technical and medical knowledge and skills regarding, at a minimum, safety procedures and patient safety. People using the software must have acquired such knowledge and skills during their curriculum.

Application training: Application training is delivered with the software installation according to the handover contract. It is mandatory to follow such application training delivered by Siemens Healthineers Representative before any use of the system. The follow-up training, which is necessary due to change of personnel, is in the responsibility of the operator of the system. Any additional training can be requested from Siemens Healthineers.

## 3.3 Preclinical evidence

N/A since all medical devices including software are CE marked and are used according to the approved intended use.

*See Appendix C- US Protocol Amendments

## 3.4 Clinical Evidence to Date

### 3.4.1 Systematic review: Search strategy

We conducted a systematic review of the existing evidence on bleeding detection with cranial non-contrast syngo DynaCT Sine Spin imaging and cranial non-contrast FDCT imaging in general. We searched Embase (via Elsevier), Medline (via Ovid), and the Cochrane Central Registry of Controlled Trials (CENTRAL) (date of last updated search March 23, 2022). The latter includes the trial registries clinicaltrials.gov and the World Health Organization International Clinical Trials Registry Platform (WHO ICTRP) search portal. Search strings around the concept flat detector CT, cone beam CT, head and cranial were composed of database-specific subject headings (where applicable) and text word synonyms. The search was confined to the time period from 2016 till now (January 2022) since the triage of stroke patients with FDCT was first described in 2017.^10^

### 3.4.2 Clinical evidence to Date

We screened 4,950 records, out of which one evaluated non-contrast syngo DynaCT Sine Spin for the detection of intracranial haemorrhage.^6^ Furthermore, we found a few publications evaluating non-contrast cranial FDCT imaging in general for bleeding detection.^18, 42, 43^ The two most recent publications found very high sensitivities for the detection of intraparenchymal or intraventricular haemorrhage (97-100%) but only moderate to high sensitivity for the detection of subarachnoid haemorrhages, especially in the posterior fossa.^6, 42^

However, all these studies had important methodical issues. Most importantly, only a minority of patients came from the most relevant patient group: suspected stroke patients presenting with a spontaneous intraparenchymal and/or intraventricular haemorrhage. They mainly used surrogate patients, as they included patients which developed an intraparenchymal and/or intraventricular haemorrhage after an intervention. Findings from these patients cannot be generalized to patients presenting with a spontaneous intraparenchymal and/or intraventricular haemorrhage as haemorrhage location, size and distribution might differ substantially. An analysis of the Swiss Stroke Registry of patients from the University Hospital Basel showed that in our targeted patient population (suspected acute stroke patients with an NIHSS ≥7) 16% presented with such a spontaneous haemorrhage. Secondly, the studies did not define the patient population prospectively but rather used all patients available for their analysis. Therefore, the reported sensitivities and specificities could not be generalized to our targeted patient population (patients presenting with symptoms suggestive of a severe acute ischemic stroke or an intracranial bleeding). Third, in some of their cases an FDCT which was done prior to an intervention was compared to an MDCT which was done after the intervention. In these cases, it is not always feasible to deduce, if a bleeding occurred due to the intervention or was missed in the first scan. Also, due to the retrospective nature of the studies selection bias could not be ruled out.

## 3.5 Justification for the design of the clinical investigation

Clinical evidence based on the so far conducted studies is insufficient due to multiple reasons:

a) the most important patient group (suspected stroke patients with a spontaneous intraparenchymal and/or intraventricular hemorrhage) was underrepresented in the aforementioned studies,

b) the studies were retrospective with unclear patient enrollment criteria,

c) the studies had low sample sizes and

d) they used different (outdated) systems for the acquisition of cranial FDCT images.

To address all these issues, we propose performing a cross-sectional non-inferiority investigation with prospective open label data collection and blinded endpoint assessment. Using this design enables us to generate high quality data for the estimation of the sensitivity and specificity of non-contrast syngo DynaCT Sine Spin imaging for the detection of intracranial hemorrhages. It will allow clinicians in the future to make evidence-based decisions regarding the ability of cranial FDCT imaging to detect intracranial hemorrhages in suspected acute ischemic stroke patients. To ensure high external validity of our findings, the enrolled patient population will closely assemble the patient population undergoing cranial FDCT imaging in the future.^11, 12^

Non-contrast syngo DynaCT Sine Spin imaging was chosen as it is already used in clinical practice for the triage of suspected stroke patients. It will be used in the same way as in clinical routine. We will not deviate from its intended use and there will be no deviation from the imaging protocols already used in clinical routine for the detection of intracranial hemorrhages. The main endpoints will be the sensitivity and specificity of non-contrast syngo DynaCT Sine Spin imaging for the detection of intracranial hemorrhage.

## 3.6 Explanation for choice of comparator/ground truth

To calculate the sensitivity and specificity of non-contrast syngo DynaCT Sine Spin imaging a ground truth must be defined. The ground truth will be defined based on the MDCT images from the same patient. MDCT was chosen as the reference standard for the following reasons:

(1) It is standard of care in most hospitals worldwide for the detection of intracranial hemorrhages in acute stroke patients.^19, 44^

(2) It was identified as the gold standard for the detection of intracranial hemorrhages by the American Heart Association/American Stroke Association (AHA/ASA).^19, 44^

(3) It has very high sensitivities for the detection of intracranial hemorrhages. Recent studies yielded sensitives of 99.7% to 100% for the detection of subarachnoid hemorrhages (SAHs), even in non-academic centers.^45-47^

## 3.7 Risk evaluation (Risk-to-Benefits rationale)

Anticipated adverse device effects and residual risks associated with the MD and the procedures involved in its use:

**Ionizing radiation:**

Anticipated adverse device effects include risks related to effects of ionizing radiation. Biological hazards of ionizing radiation include deterministic effects like skin burns (erythema), cataracts, (permanent) epilation, (delayed) skin necrosis and death. Stochastic hazards of ionizing radiation like x-rays include genetic defects that can lead to cancer or hereditary diseases. The radiation dose typically applied during the intervention in this clinical investigation is related to the performance of a syngo DynaCT Sine Spin non-contrast scan protocol for the detection of intracranial bleeding. The typical effective dose during this scan is up to 2.5 mSv (according to internal measurements and recent publications).^3, 6^

The risks related to ionizing radiation can be minimized by reducing the X-ray exposure to the necessary minimum. This is done by following the ALARA principle and by careful and systematic application of protection measures for the patient, the operator and the clinical staff which are described in detail in the instructions for use, section 3.16.

**Skin irritations:**

Skin irritation may occur due to long-term skin contact especially in the presence of chemical residues e. g. that of cleaning / disinfection substances. This risk is inherent to any medical procedure and patient contact is limited to sterile disposable sheets and cleaning instructions are provided in the instructions for use.

**Pressure necrosis:**

Pressure necrosis may also occur while the patient is in the examination position. The patient table and patient positioning devices allow patient positioning that reduces the risk of pressure necrosis. During long examinations, trained personnel is required to minimize the risk of pressure necrosis by adequate means e. g. decubitus prophylaxis while the patient remains in examination position. As the intervention itself the non-contrast cranial syngo DynaCT Sine Spin does only take 7 seconds for acquisition of the images and a maximum timespan of 3 minutes for the conduct including patient positioning, pressure necrosis due to the FDCT scan is highly unlikely. Furthermore, in case of an ischemic stroke due to a vessel occlusion or another treatable cause of stroke, the treatment itself will take far longer than the scan itself.

**General risks associated with the medical device:**

Further risks associated with the device include typical risks associated with medical imaging equipment, e. g. collisions during system movements, or system failures and are described in detail in the instructions for use. Precautions and warnings as well as preventive measures are implemented and also described in the instructions for use.

Although the subjects in our investigation have no direct clinical benefit from participating in this clinical investigation, it might be highly relevant for future suspected acute ischemic stroke patients. As outlined above the demonstration of adequate diagnostic power of non-contrast syngo DynaCT Sine Spin for the detection of intracranial hemorrhage will very likely lead to a more widespread implementation of direct to angiography approaches. In 2016 MT was performed in 27,576 patients in Europe and projections estimate that roughly 200,000 patients were eligible for MT (numbers taken from the 2016 European Stroke Organization, European Academy of Neurology and Stroke Alliance for Europe survey), highlighting the outstanding high patient numbers, who could potentially profit from this clinical investigation.

The risk to subjects in our investigation is minimal. As in our investigation all patients undergo both MDCT and FDCT imaging for the detection of intracranial hemorrhage, there is no foreseeable scenario in which an important diagnosis (i.e., if there is an intracranial hemorrhage) would be overseen due to enrollment into the investigation. All clinical decisions should be based on the initial MDCT scan and not on the FDCT scan. Furthermore, only patients in whom no invasive procedure for immediate treatment is planned between both scans are eligible, ruling out the risk of treatment delay due to participation in the study. The performance of a syngo DynaCT Sine Spin scan is clinical routine in most of the enrolled subjects. In subjects presenting with an acute ischemic stroke (50% of the subjects) or a SAH (5-10% of the subjects) a baseline syngo DynaCT Sine Spin scan prior to the intervention is done in clinical routine on a case-to-case basis to rule out the occurrence of new bleedings or worsening of the SAH. In subjects presenting with an intraparenchymal/intraventricular hemorrhage (approximately 40-45% of the subjects) the FDCT scan is not always done in clinical routine.

In subjects who would normally not undergo a syngo DynaCT Sine Spin scan, there is a foreseeable risk due to minor excess radiation (up to 2.5 mSv according to measurements from Siemens Healthineers and recent publications).^3, 6^ This is like the average yearly radiation from artificial sources. Deterministic radiation damage is very unlikely since the average dose of the used protocol is far below established thresholds. This statement extends to the skin entrance dose. Internal safety systems of the MD under investigation, prevents any deterministic radiation damage.

Treatment delays due to the syngo DynaCT Sine Spin scan will be negligible, as the patient positioning on the angiography table is identical for the syngo DynaCT Sine Spin as for the following intervention. Therefore, the net treatment delay in patients not routinely undergoing syngo DynaCT Sine Spin is under 1 minute (time for acquisition of the syngo DynaCT Sine Spin is 7 seconds).

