The value of the proposed clinical investigation lies in the validation of a new imaging modality for suspected acute stroke patients, which might allow in the future to triage severely affected stroke patients faster (studies point to a time gain of approximately 30 minutes).^11-13^ This might ultimately lead to better clinical outcomes in this often severely affected patient group, which would lower their burden of disease substantially.^9, 14, 22-25^ As stroke is still one of the leading causes of mortality and disability worldwide,^26-28^ this could have relevant effects on socioeconomic costs as well.^29^ (see section 3.1) The proposed clinical investigation will be the first investigation evaluating the non-contrast syngo DynaCT Sine Spin imaging protocol for the detection of acute, spontaneously occurring intracranial hemorrhage prospectively and with blinded outcome assessment, guaranteeing high validity of the findings. Furthermore, patients will be enrolled based mainly on clinical features (i.e., their symptoms), guaranteeing that the population enrolled within this clinical investigation, resembles the patient population which undergoes the procedure in everyday practice. The syngo DynaCT Sine Spin scan will be done as in standard clinical practice. This guarantees high external validity of our findings (see section 6). As pointed out subject selection will be done in close accordance with the patient population, which would undergo this procedure in everyday clinical practice (see section 7). Treatment delays due to the syngo DynaCT Sine Spin will be negligible, as the patient positioning on the angiography table is identical for the syngo DynaCT Sine Spin as for the following intervention. Therefore, the net treatment delay in patients not routinely undergoing syngo DynaCT Sine Spin is below 1 minute (time for acquisition of the sine spin FDCT is 7 seconds). In most of the subjects the second syngo DynaCT Sine Spin is clinical routine as it is often used to obtain a baseline status of the subject after transport to the angiography suite. This is done for example to rule out new or worsening hemorrhages prior to the intervention. In some subjects presenting with an intraparenchymal/intraventricular hemorrhagethe syngo DynaCT Sine Spin scan is not usually done in clinical routine. These subjects will receive minor extra radiation (up to 2.5 mSV) as in these patients the syngo DynaCT Sine Spin would not be done in clinical routine. ^6^

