The FDCT readings of the six core-lab readers will be compared with the ground truth and based on this comparison they will be rated as true positive, true negative, false positive or false negative. This will be done separately for each reader. In case most of the first core-lab readers (at least 5 out of 6) detect a hemorrhage on the FDCT scan, which according to the ground truth was no present on the MDCT scan, the second core-lab will use all available images and clinical data (unblinded) to decide if there is any evidence for the hemorrhage to have occurred between the MDCT and FDCT scans (always a possibility in patients with a stroke, e.g., without a hemorrhage on MDCT, treated with iv-lysis and then with a hemorrhage on FDCT as a complication of intravenous lytic treatment). In this case the patient will be excluded from further analysis. See table 2 for a detailed overview of all possible constellations:

| Ground truth | Core-Lab 1 | Core-Lab 2 | Final Result |
| --- | --- | --- | --- |
| MDCT | FDCT | FDCT | FDCT |
| (+) | (+) | NA | True (+) |
| (-) | (-) | NA | True (-) |
| (+) | (-) | NA | False (-) |
| (-) | (+) | (-) | False (+) |
| (-) | (+) | (+) | Hemorrhage occurred between scans |

Table 2. Overview of possible outcomes for the FDCT readings

Based on the results the sensitivity and specificity of non-contrast syngo DynaCT Sine Spin for the detection of hemorrhages will be calculated.

We chose this design approach for the following reasons:

1. The only way to benchmark the diagnostic performance of non-contrast syngo DynaCT Sine Spin imaging for the detection of intracranial haemorrhage is to compare it to the gold standard, which is cranial non-contrast MDCT imaging.^19, 44^ Therefore, it is of pivotal importance that scans of the same person, which were acquired under comparable conditions are used. This is ensured by the facts that (a) only patients in whom no invasive procedure between both scans is planned can be enrolled and (b) that the time period between both scans is under four hours. Using these criteria, it is highly unlikely, that new bleeding events occur between both scans. However, to account for the very low possibility of an early bleeding due to intravenous lysis, which would occur after the MDCT but before the FDCT, a second core-lab was implemented to identify these cases.

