## 7.2 Recruitment and screening

Recruitment takes place in an emergency setting through usual care. No additional screening or examinations (except in women with child-bearing potential a pregnancy test) compared to normal clinical practice are necessary. The MDCT will be performed completely independently from the study.

All patients presenting to one of the participating sites with symptoms suggestive of acute stroke (i.e. NIHSS ≥7) or of an intracranial hemorrhage should be screened for this trial. In case of patients referred from other hospitals they are only considered for participation in this trial if they have an indication for repeated imaging according to local standards of care. For clarification repeated imaging can be done with FDCT, if external MDCT was of sufficient quality, is in the PACS of enrolling center, was within 4 hours of the anticipated FDCT, and the clinical presentation of the patient has not substantially changed (i.e., increase of NIHSS of more than 4 points). Patients will be recruited in the emergency or MDCT room. Primary responsibility for recruitment of patients will lie with the PI at each site.

Patients will not receive compensation for taking part in the trial.

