### 8.1.2 Control Intervention (standard/routine/comparator)

The control intervention is a non-contrast cranial MDCT scan. The system for the scan is left at the discretion of the site investigator. It is standard of care and done in all subjects irrespectively of their participation in the clinical investigation.

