### 9.3.2 Visit 1 - Intervention

Treatment will be continued for all subjects according to the international AHA/ASA guidelines^44^ and according to local standard practice.

After eligibility has been confirmed, the responsible investigator will access a 24-hour password protected, internet-based enrolment system to enrol the subject into the clinical investigation. The patient will be transported immediately to the angiography suite for subsequent treatment or further diagnostics. In the angiography suite non-contrast cranial syngo DynaCT Sine Spin imaging must be performed within four hours after the MDCT scan and before any other intervention or operation.

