## 11.2 Determination of Sample Size

To calculate the sample size, hypothetical experiments were simulated. We estimate a sensitivity of 99% and a specificity of 98% of non-contrast syngo DynaCT Sine Spin imaging for the detection of intracranial hemorrhage as it was described for the predecessor generation in the literature.^48^ To account for variation, diagnostic performance of hypothetical readers was varied with rates of 98.5%, 99% and 99.5% for sensitivity and 97.5%, 98% and 98.5% for specificity. Rates were attributed randomly with equal chance.

Sensitivities and specificities of readers were generated from correlated binary random variables. To reproduce the correlated readings between readers, a high correlation between binary random variables was chosen. This assumption was made based on the literature and judgement of the principal investigators. We further simulated lower correlations which showed consistently that an approach using a high correlation is more conservative (i.e., leading to a higher sample size). Generated outcomes were vectors with 1 (true positive) and 0 (false negative) for sensitivity and 1 (true negative) and 0 (false positive) for specificity. The quotient of the occurrences of 1 and the number of cases with/or without a bleeding being sensitivity and specificity, respectively. In case sensitivity or specificity was 100%, a false negative (for sensitivity) and a false positive (for specificity) was introduced into the generated output. This enabled to still fit a model (see below).

To represent “difficult cases”, i.e. patients who present with an isolated infratentorial intracranial hemorrhage, we introduced a subpopulation of patients for whom the performance of raters was only 70% sensitivity. We chose n = 14 patients based on an additional sample size calculation. With this subsample, there is an 80% chance (power) that the lower bound of the 95%-CI of a sensitivity of 70% is higher than 50%. However, we assume that the subsample substantially overrepresents the incidence of difficult cases in the study population (see section 6.1). Therefore, we attributed a lower weight in the model to each difficult case.

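### Section 3.7 advises that every clinical decision rest on the initial MDCT and not the FDCT, which is too broad beside the FDCT's stated use to rule out new bleeding and as repeat imaging in transfer patients

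*Protocol*

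**What the plan says.** Section 3.7, under the general risks of the device, first reassures the reader that enrolment cannot cause an important diagnosis to be missed, since every patient has both scans. It then adds: "All clinical decisions should be based on the initial MDCT scan and not on the FDCT scan".

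The same paragraph says that in ischaemic stroke and subarachnoid haemorrhage (SAH) a baseline FDCT before the intervention is done in routine care, case by case, "to rule out the occurrence of new bleedings or worsening of the SAH". Section 2 gives the same purpose: "This is done for example to rule out new or worsening hemorrhages prior to the intervention".

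Section 7.2 admits transfer patients only if local standards call for repeat imaging, and clarifies that "repeated imaging can be done with FDCT, if external MDCT was of sufficient quality, is in the PACS of enrolling center". The external MDCT must also fall within 4 hours of the planned FDCT, and the patient must not have changed substantially.

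Section 6.1 describes a patient "without a hemorrhage on MDCT, treated with iv-lysis and then with a hemorrhage on FDCT as a complication of intravenous lytic treatment". It does so to explain when the second core lab removes a case from the analysis.

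On care at the visit itself, Section 9.3.2 says: "Treatment will be continued for all subjects according to the international AHA/ASA guidelines", together with local practice. It does not mention what to do with an FDCT finding.

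**The concern.** A scan done to look for new bleeding before an intervention is done to inform a decision. Advice that all decisions rest on the earlier scan, and none on this one, takes that purpose away if it is followed to the letter. The finding it would set aside is new or enlarged blood just before the intervention. The protocol treats this as rare, but it matters for safety.

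The tension is sharpest in transfer patients. There the MDCT may be an outside scan up to 4 hours old, and the FDCT may be the repeat scan that local standards called for. Taken literally, the advice prefers the older scan to the one obtained because an update was indicated.

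Nothing statistical is at stake. The issue is whether a risk-benefit section, which ethics committees read, should contain advice that is wider than its evident purpose.

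**Working it through.** The point rests on comparing statements within the protocol. There is no planned figure to reproduce.

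**Comparison of the text**

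1. *Scope of the advice (3.7).* It covers all clinical decisions, is phrased as a recommendation, and carries no exception there or elsewhere in the protocol.
2. *Routine purpose of the FDCT (2 and 3.7).* It is to rule out new or worsening bleeding before the intervention. Section 3.5 adds that the FDCT is used as in clinical routine. The broad advice and this purpose cannot both be followed when the FDCT shows new blood.
3. *Transfer patients (7.2).* The FDCT is allowed, not required, as the repeat imaging. Where it is used that way, the advice sets aside the indicated scan. A repeat MDCT is not forbidden.
4. *Between-scan bleeding (6.1).* The passage concerns endpoint adjudication. It shows that the event is foreseen, but it gives no management rule and regards the event as very unlikely.
5. *Care at the visit (9.3.2).* Guidelines and local practice govern. This softens the conflict without being a written exception.
6. *Deterioration exclusion (7.1).* It applies to an NIHSS rise of more than 4 points, so a new bleed with a smaller change is not removed by it.

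**Size of the group concerned (not a risk)**

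Inputs from 3.7: ischaemic stroke 50% of subjects, SAH 5% to 10%. Planned total from 11.2: 252.

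- Lower: 50% + 5% = 55%; 0.55 × 252 = 138.6, about 139.
- Upper: 50% + 10% = 60%; 0.60 × 252 = 151.2, about 151.

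So about 139 to 151 subjects belong to the groups in which the FDCT is described as a case-by-case bleed check.

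**The opposite error**

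Section 11.2 states: "We estimate a sensitivity of 99% and a specificity of 98% of non-contrast syngo DynaCT Sine Spin imaging". Simulated readers vary from 97.5% to 98.5% specificity. Among the 126 patients planned without haemorrhage, expected false positives per reader = 126 × (1 − specificity):

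- at 98.5%: 126 × 0.015 = 1.89;
- at 98%: 126 × 0.020 = 2.52;
- at 97.5%: 126 × 0.025 = 3.15.

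These are design assumptions for core-lab readers working to a 90-second limit, so they are only indicative for site clinicians. Contrast on the FDCT (9.2) and lesions that mimic bleeding (Appendix B) are also provided for. A bleed seen only on FDCT can therefore be false, and the replacement text should prompt clinical assessment and not automatic action.

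**Not computable.** The protocol gives neither a between-scan bleeding rate nor a number of transfer patients, so no count of affected patients follows.

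**The case against.** The strongest reply is that the sentence is being read out of its setting. It supports the claim just before it, that enrolment cannot cause a missed diagnosis, and it sits in a rationale and not in a visit procedure. Care is left to guidelines and local practice in 9.3.2, and clinicians would probably act on a new bleed. FDCT accuracy is also what the trial sets out to test, so caution about relying on that scan is a reasonable safeguard.

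Most of this stands and limits the severity. It does not remove the point, because the intended meaning can be kept in a narrower sentence and no written exception covers the uses in 2, 3.7 and 7.2.

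A reader might infer three stronger things that the protocol does not support:

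- *That sites are forbidden to act on a new bleed, or would commit a deviation by doing so.* The wording is advisory, and 9.3.2 leaves care with the treating team.
- *That participation costs patients a scan.* Section 8.1.2 says of the MDCT: "It is standard of care and done in all subjects irrespectively of their participation in the clinical investigation". For patients who present directly, the reassurance in 3.7 holds. It is weakened mainly for transfer patients whose indicated repeat scan is the FDCT.
- *That 139 to 151 patients are at risk.* That is a diagnostic group in which the FDCT is used case by case, not a count of bleeds.

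It is also tempting to require a confirmatory MDCT. That would add dose and could send a patient from the angiography suite back to CT before thrombectomy. Sections 3.1 and 3.7 stress how much delay matters and promise that the study adds almost none.

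**Conclusion.** The advice in Section 3.7 is broader than its likely purpose and conflicts, as worded, with the FDCT's stated routine use before the intervention and its permitted use as repeat imaging in transfer patients. The conclusion rests on the text alone: no exception is written, and the uses in 2, 3.7 and 7.2 are explicit.

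Severity is low. The sentence is advisory, operative care follows guidelines and local practice, and the protocol regards new bleeds between scans as very unlikely. The size of any clinical effect is unknown. The endpoint, ground truth, second core-lab exclusion, sample size and primary analysis are not touched.

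**What to change.** Replace the sentence in Section 3.7 with:

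> The initial diagnosis rests on the MDCT, and the FDCT must not be used to discount a haemorrhage seen on the MDCT. A suspected new or enlarged haemorrhage on the FDCT, including an FDCT done as indicated repeat imaging, is reported at once to the treating team and managed under local practice.

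Add a cross-reference to it in Section 9.3.2. Do not make a confirmatory MDCT a protocol rule; leave confirmation to the treating team.

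Cost: two sentences and one cross-reference, with no extra patients, study data or analysis. The downside is that a false-positive FDCT may occasionally prompt a clinical review that the present wording would discourage.
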